## Abstract

We hypothesize that the control of tongue position using a newly developed tongue position retainer, where the tongue is held in a protruded position (i.e., intervention A) or in its resting position (i.e., intervention B), is effective for maintaining upper airway patency in obstructive sleep apnea (OSA) compared with no control of tongue position. This is a randomized, controlled, non-blinded, crossover, and two-armed trial (i.e., sequence AB/BA) in 26 male participants (i.e., sample size) who are scheduled to undergo a dental operation under intravenous sedation with OSA (10 ≤ respiratory event index < 30/h). Participants will be randomly allocated into either sequence by a permuted block method, stratified by body mass index. Under intravenous sedation, participants will undergo two interventions, separated by a washout period after receiving intervention A or intervention B using a tongue position retainer after baseline evaluation, before each intervention is provided. The primary outcome is the abnormal breathing index of apnea as determined by the frequency of apnea per hour. We expect that, compared with no control of tongue position, both intervention A and intervention B will improve the abnormal breathing events with superior effects achieved by the former, offering a therapeutic option for OSA.

## 1. Introduction

The excitability of hypoglossal motoneurons innervating the genioglossus muscle, the main tongue protruder, is markedly suppressed during sleep in both healthy subjects and patients with obstructive sleep apnea (OSA) [1]. However, during wakefulness, apneic events hardly ever occur, regardless of the presence or absence of such episodes during sleep, because the genioglossus muscle reflectively augments its activity as needed to maintain the tongue in position to protect the upper airway patency [2]. Based on this phenomenon, we hypothesized that OSA could be alleviated if the resting tongue position during wakefulness can be maintained during sleep independently of genioglossus muscle activity [3].

In exploratory studies, we demonstrated that the maintenance of resting tongue position by continuous tongue suction improved OSA [3,4]. However, in subsequent trials, we also experienced treatment failure with a larger tongue; although the tongue appeared to be held throughout the night by tongue suction, the device likely allowed for the tongue base to collapse. This could indicate that not only maintaining resting tongue position per se, but also additional tongue protrusion, might mitigate tongue collapse more efficiently in OSA patients, who generally have larger tongues in comparison with non-OSA people [5,6,7,8]. Accordingly, the objective of this study is to test the following hypothesis (Figure 1); Compared with no control of tongue position, holding the tongue in a protruded position and in its resting position will improve the abnormal breathing events, with superior effects being achieved by the former in OSA patients. We designed a randomized controlled trial (RCT) to investigate the effects of controlling tongue position using a newly developed tongue position retainer (TPR) on upper airway patency in OSA during intravenous sedation. Our concept may lead to the development of different approaches to continuous positive airway pressure (CPAP) and mandibular advancement devices for OSA.

## 2. Materials and Methods

### 2.1. Study Design

This is a randomized, controlled, non-blinded, crossover, and two-armed (i.e., sequence AB/BA) clinical trial that will follow the CONSORT 2010 statement, providing an extension to randomized crossover trials to better report the results [9]. An overview of the study is presented in Figure 2, following the recommended template for the schedule of enrollment, interventions, and assessments described by Standard Protocol Items: Recommendation for Interventional Trials (SPIRIT) [10]. Recruitment will last from the day the data are released by the Japan Registry of Clinical Trials (jRCTs) (032220040) (25 April 2022), and the duration of the study itself will start from the day the data are released by jRCTs until 31 March 2026.

### 2.2. Ethical Considerations

The protocol for the present study was submitted to and approved by the institutional ethics committee at the Showa University Clinical Research Review Board, Tokyo, Japan (protocol version 1.1, approval no. S11). After this approval, the study was registered as an RCT in jRCTs on 25 April 2022, which was further amended on 26 December 2022 (protocol version 1.3). Full details of all protocol amendments are provided within the protocol (https://jrct.niph.go.jp/en-latest-detail/jRCTs032220040: accessed on 28 May 2023). All the participants will be informed of the underlying principles, the purpose of the trial with respect to the intervention, and possible slight discomfort of the tongue capsule and will provide their written consent before the initiation of the study. In addition, this study will be conducted in accordance with both the amended Declaration of Helsinki and the Clinical Trials Act [11].

### 2.3. Participants

#### 2.3.1. Inclusion Criteria

(1)Patients who are scheduled to undergo a dental operation under intravenous sedation at Showa University Koto Toyosu Hospital.(2)Males aged > 20 years.(3)Patients diagnosed with OSA [10/h ≤ respiratory event index (REI) < 30/h] based on out of center sleep testing (OCST; also referred to as home sleep apnea testing or type III portable monitoring) (PMP-300E, Pacific Medico Co., Ltd., Tokyo, Japan) [12,13,14,15]. Assessment will be performed by registered polysomnographic technologists in accordance with the American Academy of Sleep Medicine Scoring Manual [16].(4)Patients who are healthy, or who have mild systemic disease in accordance with American Society of Anesthesiologists physical status I or II [17].(5)Patients who agree to participate in this study and provide their written consent to participate in the study.

#### 2.3.2. Exclusion Criteria

(1)Patients with cognitive dysfunction and/or sensor impairment.(2)Subjects assumed to be ineligible by the principal investigator or co-investigators.(3)Patients who cannot provide their written consent.(4)Patients in whom the tongue cannot be maintained in position by the TPR.

### 2.4. Intervention

Control of tongue position during intravenous sedation will be performed using a TPR. The TPR consists of five parts: (1) tongue capsule (SK Corporation Ltd., Tokyo, Japan), (2) tube made of silicone (SK Corporation Ltd., Tokyo, Japan) (3) adapter made of polyacetal that connects the tongue capsule to the tube, (4) vacuum syringe to generate negative pressure (10 mL, VACKLOK, Merit Medical Japan, Tokyo, Japan), and (5) stopper situated in front of the upper and lower lips to hold the tongue capsule (CGK, Tokyo, Japan) (Figure 3). Once the tongue is sucked by the light negative pressure produced by the vacuum syringe, the plunger design of the syringe should maintain the negative pressure with ease and will not inadvertently disengage. The stopper is firmly placed on the silicone tube, which prevents dorsal displacement of the tongue capsule via the tube. The tongue position is maintained as long as the tongue does not fall from the capsule. Since the investigator can position the stopper at a freely selected location on the tube, the tongue will be advanced by decreasing the distance between the stopper and the tongue capsule. In addition, the amount of tongue protrusion can be easily calibrated as a change in the distance between the stopper and the tip of the tongue capsule.

TPR will allow for tongue collapse if subjects solely wear the TPR (Figure 1a). On the other hand, resting tongue position maneuver with TPR is assumed for intervention B, and instead the tongue is held with the TPR at its resting position, where the tip of the tongue capsule is situated at the edge of the mandibular incisors (MAX 0) (Figure 1b). The tongue protrusion maneuver for intervention A is defined as holding the tongue without any soreness or discomfort using the TPR at 50% of the maximum tongue-advanced position (MAX 50) following holding the tongue using the TPR at the maximum tongue-advanced position (MAX 100) (Figure 1c).

### 2.5. Sample Size and Allocation Concealment Mechanism

In a previous study that evaluated the effect of tongue protrusion using a tongue-stabilizing device on the severity of OSA, Apnea Hypopnea Index (AHI) improved from 21.8 ± 8.6/h to 9.3 ± 5.8/h [18]. This indicates that, if intervention B is applied to a participant, there should be no change in AHI. Therefore, our null hypothesis is that the mean AHI was not different between intervention A (μ1) and intervention B (μ2) (i.e., μ1 = μ2), whereas the alternative hypothesis is that the mean AHI of intervention B is greater than that of intervention A (i.e., μ1 < μ2). The effect size (Δ0) and the power (i.e., 1-β) should be calculated with the following formula: Δ0 = (μ1 − μ2)/σ, 1 − β = Pr{t0 < −t(φ, 2α)}, φ = n1 + n2 − 2, where σ is the population standard deviation, β is the Type II error, φ is the degree of freedom, α is the Type I error set at 0.05, n1 is the number of subjects with intervention A, and n2 is the number of subjects with intervention B. Statistically, n1 and n2 are assumed to be equal (i.e., n1 = n2) to each other and 1-β is set at 0.80. Consequently, each intervention group needs 9 participants (i.e., 18 participants for both groups). If the drop-out rate is set rather high, at 30%, the study needs 25.7 samples; thus, a total of 26 participants will be required to test the hypothesis.

These 26 participants are to be randomized by creating a computer-generated randomization list using the permuted block method (Mujinwari, https://mujinwari.biz, Iruka-system, Tokyo, Japan: accessed on 28 May 2023) with random block sizes of two or four, stratified by body mass index (<25 kg/m^2^ or 25 kg/m^2^≤). Consequently, participants will be assigned random numbers based on consecutive enrollment into either sequence AB or sequence BA, which provides an approximately one-to-one ratio for the number of subjects in the two sequences.

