
A great advantage of the TPR compared to CPAP and mandibular advancement devices is that the TPR does not require either positive airway pressure or mandibular advancement. Thus, TPR can avoid the adverse effects associated with the use of CPAP (e.g., nasal congestion, nosebleeds, claustrophobia, difficulties falling asleep, discomfort due to the interface, dryness, and skin and eye discomfort) and/or mandibular advancement devices (e.g., hypersalivation or decreased saliva production, pain and discomfort in the teeth and gums, occlusal abnormalities when waking up, and discomfort in the jaw muscles and temporomandibular joint) and can be used in patients who are contraindicated for CPAP and mandibular/tongue advancement devices [28]. Moreover, another prominent merit of the TPR is that it allows for jaw movement and oral breathing. The TPR is similar to tongue-retaining devices, including the tongue-stabilizing device, in that it directly approaches the tongue for OSA treatment. We believe that maintaining the tongue in position using the TPR (Figure 1b) will have a positive impact on upper airway patency compared with no control of tongue position (Figure 1a) because it alleviates tongue collapse due to the reduction in genioglossus activity. The tongue-retaining device does not have a similar effect to TPR because it is designed to hold the tongue solely in a protruded position [29]. In addition, the TPR may be more clinically practical than our prototype device for various reasons. For example, the tongue capsule made of a thin silicone material is designed to closely fit the ventrolateral surface of the tongue (Figure 3). Therefore, once the tongue is held in the tongue capsule, it does not need continuous active suction and can be maintained by the light negative pressure produced by the vacuum syringe. These modifications will help avoid problems associated with our prototype device as well as oral pressure therapy, such as dry mouth, noise due to the accumulation of saliva in the suction tube and the vacuum generator, the difficulty of applying suction pressure, and cumbersome device management, all of which would be important factors for improving long-term acceptance/adherence [3,4,30].

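### The sample size assumes the resting position (B) has no effect, which the cited study does not show and the trial's own hypothesis denies, so the stated 80% power for A versus B lacks a valid basis

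*Protocol article*

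**What the plan says.** Section 2.5 bases the sample size on "a previous study that evaluated the effect of tongue protrusion using a tongue-stabilizing device on the severity of OSA", in which mean AHI fell from 21.8/h (SD 8.6) to 9.3/h (SD 5.8). It then states: "This indicates that, if intervention B is applied to a participant, there should be no change in AHI". The contrast it powers is A against B, with the alternative that mean AHI is higher under B. The formula is a two-group t calculation, "1 − β = Pr{t0 < −t(φ, 2α)}, φ = n1 + n2 − 2", with α 0.05 and power 0.80. It arrives at 9 per intervention group, 18 in all, and 26 after 30% drop-out. No numerical difference or SD is entered in the formula.

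The rest of the article describes B differently. The Introduction's hypothesis is that, against no control, "holding the tongue in a protruded position and in its resting position will improve the abnormal breathing events", with protrusion doing better. It also reports that the investigators' exploratory studies found OSA improved when the resting position was maintained. The Discussion expects that keeping the tongue in position (the resting hold of Figure 1b) "will have a positive impact on upper airway patency compared with no control of tongue position". The Abstract and Conclusions agree, and the Figure 1 legend stresses that no control and the resting position are distinct maneuvers.

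**The concern.** Two things are wrong. First, the inference fails. A before-after change on a device that protrudes the tongue carries no information about a tongue held at rest. Second, the premise is the opposite of what the trial sets out to show.

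The premise matters because it turns the effect of protrusion against nothing into the difference between protrusion and resting position. That is the most favourable assumption for A versus B. If B works, part of the 12.5/h is shared by both interventions and the contrast that was powered shrinks. A non-significant A-versus-B result could then be read as showing that the two positions are equally good, when the trial had been sized for a difference that its own hypothesis makes unlikely.

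**Working it through.** **Inputs.** From section 2.5: means 21.8 and 9.3/h, SDs 8.6 and 5.8, α 0.05, power 0.80, 30% drop-out. From section 2.8: two-tailed tests and a Bonferroni correction. From sections 2.1 and 2.6: every participant receives both A and B. Assumed, because the article gives no value: B's share of A's effect (a quarter, half, three quarters), the within-person correlation (0 to 0.7), and three comparisons for the Bonferroni level (0.05/3 = 0.0167).

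**Step 1: reproduce the stated figure.** Difference 21.8 − 9.3 = 12.5/h. For two groups of n, the noncentrality is (12.5/8.6)·√(n/2) on 2n − 2 degrees of freedom. At two-sided 0.05, n = 8 gives 77% and n = 9 gives 82.5%, so 9 per group. Then 18/0.7 = 25.7, so 26. Other ways of using the printed AHI figures miss:
- One-sided 0.05, which is how the printed formula reads, gives 7 with SD 8.6.
- The pooled SD, √((8.6² + 5.8²)/2) = 7.33, gives 7 two-sided and 6 one-sided.
- SD √(8.6² + 5.8²) = 10.37, one-sided, gives 10 by the t formula. It gives 9 only by a normal approximation, and that route also uses the full 12.5/h.

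Together with the quoted sentence, this points to 12.5/h as the A-minus-B difference.

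**Step 2: the plan's own formula if B works.** With A's effect at 12.5/h, the A-minus-B difference is 12.5 × (1 − B's share). With 9 per group, SD 8.6, two-sided 0.05 and 16 degrees of freedom:

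| B's share | A minus B (/h) | Noncentrality | Power |
|---|---|---|---|
| none | 12.5 | 3.08 | 82.5% |
| quarter | 9.4 | 2.31 | 58% |
| half | 6.25 | 1.54 | 31% |
| three quarters | 3.1 | 0.77 | 11% |

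**Step 3: the crossover.** The SD of the within-person difference is √(8.6² + 5.8² − 2ρ·8.6·5.8), which is 10.37, 8.81, 7.60 and 6.15 for ρ = 0, 0.3, 0.5 and 0.7. The noncentrality is difference·√N/SD on N − 2 degrees of freedom. For example, half share with ρ = 0.5 and N = 18 gives 6.25 × 4.243/7.60 = 3.49 and power 91%.

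| B's share | 18 completers, 0.05 | 18 completers, 0.0167 |
|---|---|---|
| quarter | 95% to nearly 100% | 86% to nearly 100% |
| half | 67–98% | 47–94% |
| three quarters | 22–53% | 11–34% |

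In the half case at 0.05, power is 67%, 81%, 91% and 98% for the four correlations. If all 26 complete, the three-quarters case gives 31–70% at 0.05. With SD 8.6 under both interventions, 18 completers and 0.05, the ranges are 87% to nearly 100%, about 54–96%, and 18–46%.

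**The case against.** The strongest reply is that the data will not come from 9 against 9 independent patients. Each participant supplies both A and B, and the gain from pairing offsets much or all of the loss. This stands. With B at a quarter of A's effect, power exceeds 80% at every correlation tried. With B at half, it does so at 0.05 for three of the four correlations. Eighteen completers also assumes the whole 30% drop-out, which section 2.5 itself regards as high.

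Two stronger readings are therefore tempting but not supported. One is that power for A versus B must be below 80%, or that N must rise (the two-group formula would ask for 31 per group in the half case: 62, or 62/0.7 = 89 with drop-out). That treats the crossover as a parallel trial. The other is that the A-minus-B difference must be below 12.5/h. That follows only if A's own effect is no more than about 12.5/h. The figure comes from another device and from AHI, and the effect of the retainer under sedation on the primary outcome, ABI-A, is unknown.

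The Introduction also reports treatment failures in larger tongues, so a weak effect of B is conceivable. But the same section still hypothesizes an improvement under B, and a weak effect is not none.

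None of this rescues the rationale as printed. Section 2.5 makes no paired argument and gives no correlation.

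**Conclusion.** The sentence that B produces no change is a wrong inference and contradicts the trial's hypothesis, and it appears to drive the sample size. The stated 80% for A versus B is not supported by its own basis: with A's effect at about 12.5/h and B working at all, the same formula gives less, down to 58%, 31% or 11% in the assumed cases. What the 26 participants deliver in the crossover is undetermined rather than shown to be inadequate. It is probably ample if B has a quarter of A's effect, dependent on correlation and significance level at half, and below 80% throughout the range tried at three quarters.

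This rests on the inferred inputs (12.5/h, SD 8.6, two-sided 5%), on assumed shares and correlations with no source in the article, and on the AHI scale. It says nothing about power for ABI-A.

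**What to change.** In section 2.5:
- Delete the statement that B leaves AHI unchanged.
- Print the difference, SD and sidedness used, and label 12.5/h as the assumed effect of A against no control.
- State and justify a separate A-versus-B difference that allows B an effect. If no estimate exists, give a range such as a quarter to three quarters of A's effect.
- Restate the power that 26 participants (18 completers) give for A versus B, using a paired crossover formula, a stated correlation range and the significance level that will apply.

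N stays at 26, and procedures and recruitment do not change. The cost is rewording. The restated power may be less favourable than 80% if B has most of A's effect, and better if it has little.

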The predetermined random allocation order will be strictly applied to all consecutive consenting patients during the study period. The anesthesiologist ([name]) will be informed of the allocation of the participant immediately before the initiation of intravenous sedation to reduce potential bias. The anesthesiologist will provide conscious intravenous sedation by a bolus intravenous injection of midazolam (1 to 3 mg) and propofol (5 to 10 mg), followed by continuous infusions of propofol (1 to 3 mg kg^−1^ h^−1^) using the target-controlled infusion system [19,20]. After an acclimatization period for TPR (30 s), a baseline evaluation (i.e., no control of tongue position with TPR in place) will be performed (1 min) (Figure 4). Thereafter, each patient will undergo both interventions A (MAX50 for 1 min and MAX 100 for 1 min) and B (1 min) in a randomized order with a washout period (30 s) between the interventions. An ex-post evaluation (1 min) will also be scheduled after removal of the TPR, when both study sequences are complete. After the core part of the present study (i.e., baseline evaluation, interventions, and ex-post evaluation) which will take an average of 6 min, supplemental oxygen at a flow rate of 3 L/min will be provided for the scheduled dental operation.

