### 2.8. Statistical Analysis

The baseline measures will be compared with the measures obtained under interventions A and B. The normality of data will be tested by the Shapiro–Wilk test. Repeated-measures ANOVA with the Bonferroni correction for multiple testing, followed by Tukey’s honestly significant difference tests will be used as the parametric test for normally distributed data. If the data do not follow a normal distribution, a non-parametric test, the Kruskal–Wallis test with the Bonferroni correction for multiple testing followed by Dunn–Bonferroni tests, will be used. The data will be presented as either the mean ± standard deviation or median (interquartile range) for normal and non-normal distributions. All statistical analyses will be performed using SPSS software (version 25, IBM Japan, Tokyo, Japan). All *p* values are two-tailed and a *p* value of <0.05 is considered to indicate statistical significance.

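### Section 2.5 prints a one-sided, two-independent-group power calculation for a crossover analysed two-tailed, so the stated 80% power at 18 is not that of the planned comparison

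*Protocol article*

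**What the plan says.** Section 2.5 takes its effect from an earlier study of a tongue-stabilizing device, in which AHI "improved from 21.8 ± 8.6/h to 9.3 ± 5.8/h". It adds that "if intervention B is applied to a participant, there should be no change in AHI", so the before-after change of 12.5/h serves as the A−B difference.

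The hypothesis is directional: "the alternative hypothesis is that the mean AHI of intervention B is greater than that of intervention A". The critical value is written t(φ, 2α) with α = 0.05, and the degrees of freedom are φ = n1 + n2 − 2, where "n1 is the number of subjects with intervention A, and n2 is the number of subjects with intervention B". The standardized effect divides by σ, which is defined only in words ("where σ is the population standard deviation"). Power is set at 0.80. The result is that "each intervention group needs 9 participants (i.e., 18 participants for both groups", raised to 26 for 30% drop-out.

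Section 2.6 describes another structure: "each patient will undergo both interventions A" and B, in random order. Section 2.8 plans repeated-measures ANOVA with Bonferroni correction for normally distributed data and states that all p "values are two-tailed", with 0.05 as the threshold.

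**The concern.** Three features of the printed calculation do not fit the trial.

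- **Design.** The degrees of freedom and the total of 18 count each person once, under A or under B. In this trial each person contributes to both. The relevant spread is the SD of the within-participant difference, not a between-person σ.
- **Sidedness.** The printed criterion is one-sided at 0.05. The planned tests are two-tailed, with a multiplicity correction that section 2.5 does not mention.
- **Result.** With either quoted SD, or the two pooled, the printed formula does not return nine.

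At stake is the only power statement in the plan. Someone reading a null A−B result would take 20% as the designed type II error for that comparison, and the calculation does not support this.

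**Working it through.** **Inputs from section 2.5.** Means 21.8 and 9.3, so the difference is 21.8 − 9.3 = 12.5/h. SDs 8.6 and 5.8. α = 0.05, power 0.80, n1 = n2 = n. σ has no printed value, so two readings are tried: the baseline SD, 8.6, and the pooled SD, √[(8.6² + 5.8²)/2] = √(107.60/2) = 7.33.

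**Step 1: the plan's own formula.** Two independent groups, φ = 2n − 2, noncentrality Δ0·√(n/2), with Δ0 taken in absolute value and power from the noncentral t. Δ0 = 12.5/8.6 = 1.453, or 12.5/7.33 = 1.704.

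| Test | σ | Smallest n per group for 80% | Power at that n | Power at 9 per group |
|---|---|---|---|---|
| One-sided 0.05 (as printed) | 8.6 | 7 | 0.820 | 0.904 |
| One-sided 0.05 (as printed) | 7.33 | 6 | 0.864 | 0.965 |
| Two-sided 0.05 | 8.6 | 9 | 0.825 | 0.825 |
| Two-sided 0.05 | 7.33 | 7 | 0.833 | 0.924 |

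For the σ = 8.6 rows at n = 9, the noncentrality is 1.453 × √4.5 = 3.08 on 16 df. The critical value is 1.746 one-sided and 2.120 two-sided.

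The printed criterion thus gives 12 to 14 in total, not 18. For it to require 9 per group, σ would have to lie between about 9.6 and 10.2, above both quoted SDs. Among these readings, nine appears only in the two-sided test with σ = 8.6. The drop-out step reproduces: 18/0.7 = 25.7, rounded up to 26.

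**Step 2: the same inputs in the design actually planned.** The SD of the within-participant difference is √(8.6² + 5.8² − 2ρ·8.6·5.8) = √(107.60 − 99.76ρ). The correlation ρ is not given, so a range is shown. The test is two-sided with df n − 2 and noncentrality (12.5/SD)·√n. Because section 2.8 does not say how many comparisons the Bonferroni correction covers, 0.05/3 is an assumption (three pairwise comparisons among baseline, A and B).

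| ρ | SD of difference | 12.5/SD | Total n, 0.05 | Total n, 0.05/3 | Power at 18, 0.05 | Power at 18, 0.05/3 |
|---|---|---|---|---|---|---|
| 0 | 10.37 | 1.21 | 8 | 11 | 0.998 | 0.987 |
| 0.3 | 8.81 | 1.42 | 7 | 9 | >0.999 | 0.999 |
| 0.5 | 7.60 | 1.65 | 6 | 8 | >0.999 | >0.999 |

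**Step 3: what 18 or 26 completers can detect.** A paired two-sided test at 0.05 with 80% power detects a mean difference of about 0.70 within-person SDs at 18 completers and 0.57 at 26. At 0.05/3 the figures are about 0.83 and 0.67. They need no AHI input and so apply to any outcome for which a t-test on the differences is adequate.

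**The case against.** The strongest defence has four parts.

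- **Nine is not an arbitrary number.** σ is not printed, so the formula has no single answer, and the same t-test run two-sided with the quoted baseline SD gives exactly nine. Quite possibly the calculation was run two-sided, in line with section 2.8, and only the notation is one-sided. This stands. The fair statement is that nine is not reproducible from the printed criterion with either quoted SD. The text still needs correcting, because its criterion and its result do not agree.
- **The article condenses a fuller registered protocol**, where σ and the effect size may be given. This also stands, so the missing σ is not a separate fault. The design and sidedness conflicts remain, because the article states both sides of each.
- **Treating a crossover as independent groups errs on the safe side.** On the AHI inputs this is right, and it lowers the severity.
- **The multiplicity factor is the reviewer's choice.** It is, and it is labelled as an assumption above.

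A reader might infer that the trial is underpowered or that 26 is wrong. The documents do not support that: with their own AHI figures, 18 completers are more than enough. A reader might also infer that the calculation cannot be checked at all, but 9, 18, 25.7 and 26 can all be reconstructed. The opposite inference, that power for the primary outcome exceeds 0.98, is equally unsupported. Those figures concern AHI, whereas section 2.7.1 makes ABI-A primary, section 2.6 measures it in one-minute windows, and section 2.5 gives no difference or SD for it.

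**Conclusion.** The point holds as an error in the stated basis of the sample size, not in the number of participants. The 80% power at 18 belongs to a different design and sidedness from the comparison planned. Taken literally, the printed formula has power 0.90 to 0.97 at 9 per group. A two-sided crossover test on the same inputs has power of about 0.998 or more with 18 completers at 0.05, and about 0.987 or more at 0.05/3.

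These figures assume an A−B difference in AHI of 12.5/h, SDs of 8.6 and 5.8, a within-person correlation of zero or above, approximate normality and, for the last figure, three comparisons. They say nothing about power for ABI-A. Severity: should-fix, since neither N nor the conduct of the trial changes.

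**What to change.** Keep N = 26 and rewrite the sample-size paragraph of section 2.5 for the within-participant A−B contrast. It should state:

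1. the assumed A−B difference and its source;
2. the SD of the within-participant difference, with a range of correlations if it is built from the two marginal SDs;
3. two-sided α, with the number of comparisons that the Bonferroni correction covers;
4. degrees of freedom n − 2;
5. the power, or the detectable standardized difference, at 18 and at 26 completers (about 0.70 and 0.57 within-person SDs for 80% power at two-sided 0.05, paired test);
6. the assumption for ABI-A, or an explicit statement that the AHI-based figure does not give the power for ABI-A.

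The one-sided alternative and critical value should be removed or brought into line with section 2.8. The cost is one rewritten paragraph, with no extra participants and no change to procedures.
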